### Data protection

Researchers (physicians, pharmacists, nurses, and other associates) and multidisciplinary teams in LTCF will access the platform using their unique identifications. A multidisciplinary team in an LTCF can manage and view only the information on the LTCF participants to which it belongs.

### Statistical considerations

#### Sample size, power, and statistical methods

Sample size calculations for the cluster RCT were performed by the team biostatistician. The required number of participants was calculated from the primary endpoint, that is, the number of PIM users. Based on recent literature, PIM users in LTCF comprised 40.7% [6], and the expected effect difference through literature review was an odds ratio of 0.41 [11]. Calculating the sample size using Sample Size Calculator V2.0 (Health Services Research Unit, University of Aberdeen) with a two-sided significance level of 5% and 95% power, 1,430 participants are needed (715 in each group). A total of 1,672 participants (836 in each group) should be included to prevent a dropout rate of 15% (discharge, hospitalization, death, etc.).

#### Data analysis

The analysis will follow the intention-to-treat approach.

All analyses will be performed using SAS software (version 9.4; Cary, NC, USA). Statistical significance is defined as *p* < 0.05. This methodology follows the Consolidated Standards of Reporting Trials Statement (http://www.consort-statement.org/consort-statement) [12]. Interim analysis is planned at midpoint after the start of participants’ enrollment and when issues arise during the study, and missing data will not be replaced. If issues arise during the study, the study design will be modified.

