#### Blinding

Participants will not be blinded to the allocation because this is not practically or economically feasible. Moreover, given the nature of the intervention, no blinding is possible at the LTCF level or for the researchers, and only the statistician performing the analysis will be blinded; unblinding will occur only after the completion of the analysis.

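### Issue-triggered interim looks and open-ended design changes sit beside a single unqualified 5% threshold, so the plan permits data-driven decisions that the final test does not account for

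*Protocol article*

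**What the plan says.** Four statements in the protocol article bear on this point.

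- **Planned look.** Data analysis: "Interim analysis is planned at midpoint after the start of" participants' enrolment. Whether the midpoint is one of calendar time, residents or statistical information is not said.
- **Further looks and redesign.** The same sentence adds analyses "when issues arise during the study, and missing data will not be replaced". The next sentence reads: "If issues arise during the study, the study design will be modified".
- **Threshold.** Data analysis: "Statistical significance is defined as" p < 0.05, with no split between interim and final. The section on sample size, power and statistical methods works "with a two-sided significance level of 5% and 95% power, 1,430 participants are needed (715 in each group") and mentions no interim look.
- **Who knows the allocation.** Design and Blinding make the trial open-label for residents, facilities and researchers: "only the statistician performing the analysis will be blinded; unblinding will occur only after the completion of the analysis".

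No other section limits the looks or the changes.

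**The concern.** A 5% test keeps its error rate if it is done once, on a design that was not altered because of the between-arm results, or if the looks and alterations follow a rule fixed beforehand. Here the same undefined trigger starts both the extra looks and the redesign. The people placed to declare an issue can know which arm each facility is in. Nothing in the text stops a look from comparing arms, and nothing stops a change of sample size, endpoint or eligibility from following that comparison.

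At stake is the meaning of the final p-value and confidence interval. If the trial reports p = 0.03, a reader could not tell from this plan how many chances there had been to reach it, or whether the design had been steered by the results.

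**Working it through.** **1. The plan's own figure.** Inputs from the sample-size section: "PIM users in LTCF comprised 40.7"%, and "the expected effect difference through literature review was an odds ratio of 0.41"; two-sided α = 0.05; power 95%.

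- Control odds: 0.407/0.593 = 0.6863. Intervention odds: 0.41 × 0.6863 = 0.2814. Intervention rate: 0.2814/1.2814 = 0.2196.
- n per arm = [z(0.975)·√(2p̄(1−p̄)) + z(0.95)·√(p₁(1−p₁) + p₂(1−p₂))]² / (p₁ − p₂)², with p̄ = 0.3133, gives 157 residents (167 with continuity correction).
- The article gives no intracluster correlation (ICC). Residents per facility before dropout are 1,430/22 = 65. With an **assumed** ICC of 0.05 the design effect is 1 + 64 × 0.05 = 4.2.
- 157 × 4.2 = 659.4 and 167 × 4.2 = 701.4. Both need 11 facilities of 65, that is 715 per arm, as stated. Solving for the ICC without rounding to whole facilities gives 0.051 to 0.056.

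So 715 is consistent with a single two-sided 5% test and no allowance for interim looks. It does not prove this, because the ICC is unstated. The sample size is not at fault on this point.

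**2. Error rate if looks are comparative.** Assumption, not in the text: every look compares arms and a claim is allowed at each if p < 0.05. The test statistics at information fractions tᵢ < tⱼ are treated as normal with correlation √(tᵢ/tⱼ). The error rate is P(|Z| > 1.96 at any look) when there is no effect.

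| Looks (information fractions) | Two-sided type I error |
|---|---|
| Final only | 0.050 |
| 0.5, 1 | 0.083 |
| 0.25, 1 | 0.091 |
| 0.10, 1 | 0.095 |
| 1/3, 2/3, 1 | 0.107 |
| 0.25, 0.5, 0.75, 1 | 0.126 |
| five equally spaced | 0.142 |

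The half-information row is itself an assumption. If the midpoint is counted by enrolment, residents enrolled late will not yet have post-intervention data, so the fraction could be lower and the inflation slightly higher.

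**3. Error rate if only the sample size is changed.** Suppose the size is re-set on comparative interim data and the final test is left unadjusted. The worst-case one-sided error (Proschan–Hunsberger) is α + exp(−z²/2)/4 with α = 0.025 and z = 1.96: 0.025 + 0.1465/4 = 0.062.

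**4. Error rate if the looks are non-comparative.** Looks that show no between-arm outcome data leave the final test at 0.050.

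**5. What a fixed boundary would need.** One interim at half information, overall two-sided α = 0.05:

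- equal (Pocock-type) limits: p < 0.0294 at both looks;
- O'Brien–Fleming-type limits: p < 0.0052 at the interim, p < 0.0480 at the end;
- interim p < 0.001 and final p < 0.05: overall 0.0502.

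No set of limits can be computed for an open number of issue-triggered looks unless a spending function is fixed in advance.

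**The case against.** The strongest reply is that this is a condensed article. Boundaries, the purpose of the interim and the decision-makers are commonly set out in a full protocol or analysis plan, so their absence is no fault. That stands, and the point does not rest on it. It rests on what the article does state: looks triggered by undefined events, and modification without limit. No boundary held elsewhere could cover unrestricted redesign.

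Three stronger readings are tempting, and the document does not support them.

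- **That every look is tested at 0.05.** A reader might infer this from the single threshold. The text gives a general convention and never says that the interim compares arms or allows a claim. The figures in the table are therefore conditional.
- **That the interim contradicts the Blinding section.** A reader might infer that a redesign cannot wait for unblinding that comes only after the analysis. Unblinding there concerns only the statistician, who can stay masked through a pooled or A-versus-B analysis while researchers who already know the allocation decide on changes. There is no contradiction. Nor does the masking remove the problem, since a masked comparison can still be tested and acted on.
- **That redesign makes the error rate unlimited.** Type I error is bounded, and for sample-size change alone the worst case is the 0.062 above.

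It is also fair that the modification sentence is tied to issues, not expressly to interim results. The issues may be operational: Loss to follow-up already describes a facility leaving early and recruitment moving elsewhere. Knowing a facility's arm is not the same as seeing results by arm, and no section says that researchers receive such results. This is why the point concerns what the wording permits, not what the team intends.

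**Conclusion.** The point holds in this form: the Data analysis section fixes a bad rule. It allows an uncapped number of looks and unrestricted modification in an open-label trial, with one unqualified 5% threshold and a sample size set at a two-sided 5% level. The final test's error rate is then not determined by the plan.

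Its size depends on a use of the looks that the text leaves open. It is nil if they are non-comparative. It is about 8.3%, 10.7% and 12.6% for one, two and three equally spaced interims if arms are compared and a claim is allowed each time at 0.05. These values assume normal test statistics, and for the single interim half the information. With one interim at a fraction between 0.10 and 0.5, the range is 8.3% to 9.5%.

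**What to change.** Replace the clause on issue-triggered analyses and the sentence on modifying the design with wording to this effect:

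- The midpoint interim covers recruitment, attrition, safety and pooled outcome rates. There is no between-arm efficacy test, and the final test keeps 0.05.
- Alternatively, if a comparative look is wanted, its timing and boundary are fixed in advance on the endpoint used for the sample size (users of potentially inappropriate medication). An interim limit of p < 0.001 with a final limit of 0.05 gives about 0.050 overall.
- Unscheduled looks are limited to non-comparative or safety reviews, which stay allowed.
- Design changes are made only by dated amendment, for reasons not based on between-arm outcome data.

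The exact timing of the midpoint is the team's choice, but it should be stated.

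The cost is a change of wording. With the first option or the p < 0.001 limit, the final threshold stays at 0.05. What is given up is the freedom to stop or redesign on an informal comparative look.

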#### Data management and data quality

Quality assurance and control of data will be conducted in accordance with Good Clinical Practice (decisions of November 24, 2006) [13].

Participant identifiers in electronic files and paper documents will be kept strictly confidential. Electronic and paper documents will be stored for 10 years [13].

### Loss to follow-up

We anticipated a conservative maximum loss to follow-up rate of 15%. Participants lost to follow-up will be classified as such because they elected to no longer be part of any further follow-up (withdrawal of consent) or were unable to participate because of discharge, hospitalization, death, etc. In the case of discontinuation of research at an LTCF before the completion of the registration of 76 participants, the target of one cluster, participants already registered at the LTCF are included in the study for intervention and follow-up, and the remaining participants are recruited from other similarly-sized LTCFs (number of residents). In cases where participants who are lost to follow-up do not explicitly withdraw consent, medication and healthcare utilization data will still be collected from participant charts via chart audits where possible [9].

### Safety and monitoring

Details of any clinically adverse symptoms or effects at the research data collection points detected by a nurse or NH worker and reported to the researcher will be acted upon immediately and at the same time will be securely provided to their visiting physicians and pharmacist at that time. If a participant experiences a serious adverse event (SAE), the study team will notify the research ethics board of any SAE thought to be related to the study, using the standard SAE form.

## Discussion

This study protocol describes a pragmatic, cluster RCT designed to assess the effect of an MMMP in an LTCF with well-established inter-professional collaborations to ensure a reduction in polypharmacy and PIM use.

In the past decade, numerous studies have anchored the CMR and deprescribing as a safe and powerful tool to enhance clinical outcomes for older patients and NH residents [14], and have been shown to be beneficial for relevant clinical outcomes [11, 14]. However, the evidence for the effect of interventions to reduce polypharmacy and PIM use on health outcomes in LTCF settings is inconsistent and difficult to implement [9]. A study in an LTCF targeting deprescribing of anticholinergic and sedative medicines showed that medication reduction resulted in reductions in psychotropic drug side effects, falls, and depression and frailty scores [15]. However, another systematic review reported that no firm conclusions on the effects could be drawn [16]. Moreover, several reviews recommended further RCTs evaluating multidisciplinary interventions and clinical outcomes in specific high-risk populations, such as LTCF populations.

To the best of our knowledge, the impact of CMR and deprescribing has not been clarified in previous research, and it has not been determined whether negative health outcomes are reversible if polypharmacy and PIM use are reduced. In this respect, our study is novel and unique in its design, by introducing an operationalized structured clinical pathway aimed at tackling polypharmacy and PIM use in LTCF settings while simultaneously considering participants’ goals and priorities for treatment through the participation of participants and guardians. In addition, several explicit tools and deprescription guidelines are available on the platform to check medications that may be inappropriate or suitable for deprescription among LTCF residents. Furthermore, most of the ongoing studies are limited to the Americas and Europe; therefore, it is time to develop and implement programs suitable for Asian conditions, and it is necessary to confirm the clinical effects of comprehensive and systematic medication management in LTCFs through the operation of developed programs. We will also evaluate participants, guardians, and physicians’ experiences of participating in the program.

In our study, participants and researchers are not blinded due to the nature of the intervention (open-label study). To minimize the bias caused by this, we implemented cluster study design. Additionally, in order to minimize performance and detection bias, the study will be conducted according to a pre-determined method according to the protocol. Moreover, if there are indicators with significant differences between the intervention group and the control group when analyzing the results later, they will be adjusted using statistical techniques. Furthermore, in order to minimize attrition bias in the outcome analysis, we will follow the intention-to-treat approach, and data on those who dropped out will be obtained and analyzed from data of the National Health Insurance Sharing Service (It refers to a vast amount of data amounting to 1.3 trillion cases, including demographic information about each patient, details of prescribed drugs, prescribed medical tests and health checkup results, and long-term care insurance data for the elderly, of all citizens).

We developed a multidisciplinary medication management program (comprehensive medication reviews, deprescribing, and multidisciplinary case conferences) to assess its impact on medication use and health problems among LTCF residents. This program, with a high level of evidence as a study with a long-term follow-up period targeting a large population, is immediately scalable, and the results of the trial, if successful, are anticipated to be directly translatable into clinical practice [9] and will become a part of routine preventive care in LTCF residents. Evidence from this study will help to understand the provision of a systematic approach to reducing the burden of polypharmacy and PIMs, as well as providing a systematic clinical pathway for implementation. Based on our results, intervention methods suitable for other settings should be developed.

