**Methods:**

A total of 1,672 residents aged ≥ 65 years from 22 nursing homes in South Korea who meet the targeted criteria, such as the use of ≥ 10 medications, are eligible to participate. The experimental group will receive a comprehensive medication review, deprescription, and multidisciplinary case conference with the help of platform. Outcomes will be measured at baseline, at the end of the intervention, as well as at 3, 6, 9, and 12 months after the end of the intervention. The primary endpoints will be the rate of adverse drug events, number of potentially inappropriate medications/potentially inappropriate medication users/two or more central nervous system drug/ central nervous system drug users, delirium, emergency department visits, hospitalization, and falls. The secondary endpoint will be the number of medications taken and polypharmacy users.

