### Allocation and randomization

LTCF clusters will be randomly allocated in a 1:1 ratio to either the intervention or control group. A randomization sequence will be generated using a computerized system. All participants in one LTCF cluster will be assigned to the same group.

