### Endpoints/evaluation criteria

The evaluation indices comprise clinical and process evaluation indices, and the clinical evaluation indices comprise primary and secondary outcomes. Primary and secondary outcomes will be measured at baseline (T1), at the end of the intervention (T2), as well as at 3 (T3), 6 (T4), 9 (T5), and 12 months (T6) after the end of the intervention for effectiveness analysis. Figure 1 shows a detailed schedule of data collection.

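### Covariates are to be chosen by significance tests between arms at analysis time, which leaves the model data-dependent and does not secure adjustment for the T1 value

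*Protocol article*

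**What the plan says.** In the Discussion of the protocol article, among the measures meant to limit bias in an open-label trial, the plan is that "if there are indicators with significant differences between the intervention group and the control group when analyzing the results later, they will be adjusted" by statistical techniques. The term for what is tested is not defined and is not restricted to variables measured before randomisation.

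The Data analysis section names intention-to-treat, SAS and a 0.05 threshold. It gives no covariate set and no model, so the Discussion sentence is the only covariate rule in the article.

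The Endpoints/evaluation criteria section states that "Primary and secondary outcomes will be measured at baseline (T1), at the end of the intervention (T2") and then at four later visits, all for the effectiveness analysis. The Follow-up and data collection section also lists age, sex, long-term care level and medication history.

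The unit of allocation is the facility: "LTCF clusters will be randomly allocated in a 1:1 ratio to either the intervention or control group". The Abstract gives "A total of 1,672 residents aged ≥ 65 years from 22 nursing homes in South Korea", hence 11 facilities per arm.

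**The concern.** A test of difference between randomised arms asks whether chance produced an imbalance. It does not ask whether the variable predicts the outcome. A strong predictor with a moderate imbalance stays out of the model, while a weak predictor with a large imbalance goes in. The covariate set, and so the estimate and its p-value, is known only once the data have been seen. That sits badly with the sentence just before it in the Discussion, which relies on a method fixed in advance to limit bias.

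The undefined term adds a second problem. Read literally, it could admit variables measured after randomisation that the programme itself changes, and adjusting for those can remove part of the treatment effect.

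At stake are the precision that a fixed T1 adjustment could give with only 22 randomised units, and the credibility of a model that was not settled beforehand.

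**Working it through.** **Inputs from the article.** 22 facilities, 1:1; 76 enrolled per facility (Loss to follow-up); 715 evaluable per arm, so 715/11 = 65 per facility; "PIM users in LTCF comprised 40.7"%; "the expected effect difference through literature review was an odds ratio of 0.41"; two-sided 5%, 95% power.

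**Assumed, because the article does not give them.** The ICC; the correlation (rho) between facility means at T1 and follow-up; the share of variance that T1 explains.

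**1. The stated sample size.** Intervention odds = 0.41 × 0.407/0.593 = 0.2814, so the intervention rate is 0.2814/1.2814 = 22.0% and the difference is 18.7 points. An individually randomised comparison needs 157 per arm. With ICC 0.05 the design effect is 1 + 64 × 0.05 = 4.2, and 157 × 4.2 = 659. Rounding up to whole facilities of 65 gives 11 × 65 = 715, the stated figure. The size is not in dispute, and an ICC near 0.05 fits it.

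**2. What the rule leaves out.** At T1, with 76 per facility, ICC 0.05 and a prevalence of 40.7%, the design effect is 1 + 75 × 0.05 = 4.75. The chance SD of the difference between arms is √(2 × 0.407 × 0.593 × 4.75/836) = 5.2 points. A valid test on 20 df (critical value 2.086) would flag only differences beyond about 2.086 × 5.2 = 10.8 points. Smaller imbalances in T1 PIM use would go unadjusted, against a target effect of 18.7 points.

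**3. How often T1 enters, and what follows.** Simulation of 11 v 11 facility means, 200,000 runs, with the effect set to give about 80% power unadjusted. T1 enters under the trigger in 5.1% of runs.

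| rho | Power, always adjusted for T1 | Power, T1 only if p<0.05 | Type I error, triggered |
|---|---|---|---|
| 0.3 | 81.0% | 79.4% | 4.7% |
| 0.5 | 87.7% | 80.1% | 4.3% |
| 0.7 | 96.6% | 81.2% | 3.6% |
| 0.8 | 99.4% | 81.7% | 3.1% |

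Always adjusting holds type I error at 5.0%.

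**4. The same at the trial's own size.** Take SE = √{[p₁(1−p₁) + p₂(1−p₂)] × V/11}, with V = ICC + (1−ICC)/65 unadjusted and V = 0.75 × ICC + 0.90 × (1−ICC)/65 adjusted (T1 explaining 25% between and 10% within facilities). Power is from the noncentral t on 20 df. The bracket is 0.2414 + 0.1714 = 0.4127.

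| ICC | V unadjusted | V adjusted | SE unadjusted | SE adjusted | Power unadjusted | Power adjusted |
|---|---|---|---|---|---|---|
| 0.05 | 0.0646 | 0.0507 | 4.92 points | 4.36 points | 95% | 98% |
| 0.10 | 0.1138 | 0.0875 | 6.54 points | 5.73 points | 78% | 88% |

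The variance falls by 22% at ICC 0.05 and by 23% at ICC 0.10.

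**5. Dependence on the data.** If 5, 10 or 15 independent indicators are each validly tested at 5%, the chance that at least one enters the model is 1 − 0.95^K: 23%, 40% or 54%.

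**The case against.** The best defence is that the rule adds adjustment and excludes nothing. The Endpoints section assigns the T1 measurements, with the later ones, to the effectiveness analysis, so T1 may already be a covariate or a repeated measure in a model that the SAP sets out. This stands. A reader might infer that the trial has chosen imbalance testing in place of T1 adjustment, but the article does not say so. What remains is that the one rule it states does not secure T1 adjustment, and an SAP with a fixed covariate set would have to depart from that rule.

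The precision at stake may also be small. At an ICC that fits the stated size, unadjusted power is already 95%. ICC 0.10 is about double that and has no source in the article, and the variance shares are assumed. This stands as a limit on size.

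A reader might infer that a third or more of baseline variables would be flagged by chance. At 76 per facility and ICC 0.05, a test that ignored clustering would flag 37% of variables with that ICC. Nothing in the article says that the tests would ignore clustering, and a valid test flags about 5%.

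The statistician is to be blinded until the analysis is complete (Blinding section), which limits deliberate steering. It does not stop chance imbalance from setting the model.

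Finally, the sentence most naturally concerns group imbalance at baseline, so adjustment for post-randomisation variables is a possibility left open by the wording and not a stated intention. Describing baseline differences also has a real use here: allocation lists are drawn before the study starts, and nurses in unblinded facilities obtain consent, so selective recruitment could occur.

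**Conclusion.** The concern holds for the significance trigger and for the failure to limit the indicators to baseline variables. It is a stated rule, so it cannot be set aside as detail left to an SAP.

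The consequences are a model chosen after seeing the data and a loss of whatever precision T1 offers. On the assumed variance shares, that loss is about 3 points of power at ICC 0.05 and about 10 points at ICC 0.10. It is negligible if the T1 correlation is near 0.3 and large at 0.7 or above. The article does not supply the figures that would settle which applies.

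A reader might infer inflated type I error. That is not shown: with T1 as the only candidate covariate and a valid test, the triggered rule is conservative (3.1% to 4.7% for rho 0.8 to 0.3).

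**What to change.** Replace the Discussion sentence with a rule along these lines: the primary comparisons will be adjusted, whether or not the arms differ, for a short prespecified set of baseline covariates led by the T1 value of the outcome, in an analysis that accounts for clustering by facility; significance tests will not select covariates for the primary model; variables measured after randomisation will not be adjusted for.

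The T1 value should lead the set at least for the PIM and medication-count outcomes. For event outcomes such as falls or emergency visits, the article shows no look-back period at T1, so whether a T1 value is useful there should be decided in advance. Baseline differences may still be described, to detect selective recruitment, and further adjustment may be reported as a sensitivity analysis.

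The cost is a change of wording plus the decision on which covariates to name, to be made before outcome data are compared by arm. The T1 outcome values and the main resident characteristics are already collected, so no new data are needed.
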